## **2.1. Study Rationale**

The main objective is to establish whether palliative radiotherapy with 1-2 fractions of 8 Gy is non-inferior to 5 fractions of 5 Gy with respect to change in patient-reported target symptom intensity in patients with pelvic soft tissue tumors. If the main objective is achieved, and general QoL, toxicities and overall survival are comparable between the two study arms, a short-course schedule of 1-2 fractions may be recommended as standard of care, particularly beneficial for both patients with a short life expectancy and patients eligible for systemic treatment. A short-course radiotherapy schedule would also provide improved exploitation of the radiotherapy treatment capacity and reduce costs related to patient transportation and hospitalization.

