### 5.1. Inclusion Criteria

- Histologically verified primary cancer originated from gastrointestinal, urological or gynecological organs (histological verification can be performed on other lesions than the symptomatic pelvic tumor)

- Patients unsuitable for curative treatment due to either advanced disease or medical contradictions (i.e. comorbidity, old age or poor general condition)
- Primary, residual, recurrent or metastatic pelvic tumor from the abovementioned cancers not amenable for curative treatment
- Tumor-related symptoms within the following five predefined categories: pain, bleeding, bowel dysfunction, lower urinary tract dysfunction and vaginal dysfunction
- Considered as a candidate for palliative radiotherapy according to both study arms
- Patient reported average severity of symptoms  $\geq 4$  on a NRS scale of 0-10
- $\geq 18$  years of age
- Speaks and understands Norwegian or English
- Ability to understand and willing to sign a written informed consent form
- ECOG performance status of 0-3
- Expected survival  $> 12$  weeks
- Able to pause systemic cancer treatment for one week prior to, during, and one week after radiotherapy
- Women of childbearing potential (WOCBP) should have a negative highly sensitive serum pregnancy test within 72 hours prior to randomization. WOCBP must agree to the use of highly effective birth control methods or abstain from heterosexual sexual activity from randomization until completed study intervention

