### **9.2. Statistical Hypotheses**

The primary hypothesis is that a radiotherapy schedule of 1-2 fractions of 8 Gy provides non-inferior patient-reported symptomatic relief as a schedule of five fractions of 5, assessed 12 weeks after completed radiotherapy (see [Section 9.1](#) for definition of the non-inferiority margin). The lower bound of the 95% confidence interval of the difference in mean symptom intensity of arm A is therefore hypothesized to be above the non-inferiority margin of -1.

If non-inferiority regarding symptom relief, and comparable QoL, toxicities and OS can be proved 12 weeks after the intervention a short-course schedule with 1-2 fractions will be recommend as standard of care. If non-inferiority can be proven only 4 weeks after the intervention, a single fraction schedule will be recommend for patients with a very short life expectancy where palliative radiotherapy is considered reasonable.

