## 9.4. Analysis Sets

The following six analysis sets are defined:

- Intention-to-treat (ITT) set
  - All randomized participants with a signed informed consent form
- Full-analysis (FA) set
  - All randomized, eligible participants with a signed informed consent form who has received at least one radiation fraction
- Per-protocol (PP) set
  - All randomized, eligible participants with a signed informed consent form who has received the allocated radiotherapy and completed the follow-up visits at 4 and 12, and 52 weeks without major protocol deviations
- Modified PP set 1
  - All randomized, eligible participants with a signed informed consent form who has received the allocated radiotherapy and completed the follow-up visits at 4 and 12 weeks without major protocol deviations
- Modified PP set 2
  - All randomized, eligible participants with a signed informed consent form who has received the allocated radiotherapy and completed the follow-up visit at 4 weeks without major protocol deviations
- Safety set
  - All randomized participants exposed to radiotherapy

As this is a non-inferiority study, the main analysis of the primary endpoint will be based on the modified PP set 1 of participants having completed all scheduled follow-up visits at the time of assessment (12 weeks).

The main analyses of the secondary endpoints of physician-reported toxicities (CTCAE) at 4, 12, and 52 weeks will be based on the modified PP set 2, modified PP set 1, and PP set, respectively. Safety analyses of physician-reported toxicities will be based in the safety set.

The main analyses of the secondary endpoint of overall survival will be based on the FA set.

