### **9.5.3. Secondary Endpoint**

Data will be reported as means, 95 % confidence intervals, medians or frequencies as appropriate CTCAE:

For all; comparison between the two study arms

1. Number of events any grade, any CTCAE category
2. Number of events grade 1-2 vs grade 3-4, any CTCAE-category
3. Number of events any grade, by CTCAE-category
4. Number of events grade 1-2 vs grade 3-4, by CTCAE category
5. Number of patients with event, any CTCAE category
6. Number of patients with events grade 1-2 vs grade 3-4, any CTCAE category
7. Number of patients with events any grade, any CTCAE category
8. Number of patients with grade 1-2 vs grade 3-4 event, by CTCAE category

CTCAE categories: Gastrointestinal, urinary, reproductive system, constitutional, other

Overall survival:

Kaplan Meier- curves compared with the log-rank test and univariable and multivariable Cox proportional-hazards regression analyses

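### The main overall survival analysis uses the FA set, which drops randomised patients who receive no fraction or are classed as ineligible; it should use the ITT set, with vital status kept for those patients

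*Protocol*

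**What the plan says.** Overall survival is a secondary endpoint (Protocol sections 1.1 and 3). Section 9.4 assigns its analysis set: "The main analyses of the secondary endpoint of overall survival will be based on the FA set". The FA set is defined there as "All randomized, eligible participants with a signed informed consent form who has received at least one radiation fraction". The same section defines the ITT set as "All randomized participants with a signed informed consent form" but assigns it to no analysis. The remark that this is a non-inferiority study is used in 9.4 to justify a per-protocol set for the primary endpoint only. Section 9.5.3 gives the survival methods: "Kaplan Meier- curves compared with the log-rank test and univariable and multivariable Cox proportional-hazards regression analyses". No survival margin, event count or power is stated.

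Survival bears on the trial's conclusion. Section 2.1 makes the recommendation depend on it: "If the main objective is achieved, and general QoL, toxicities and overall survival are comparable between the two study arms". Section 4.2 repeats the condition, and so does section 9.2: "If non-inferiority regarding symptom relief, and comparable QoL, toxicities and OS can be proved 12 weeks after the intervention".

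Three other rules matter. Section 6.5 requires a patient in either arm to be discontinued from the study if the schedule has to be modified before radiotherapy starts. Section 7.2 ends both intervention and study participation at study discontinuation. Sections 1.1 and 4.1 censor survival at loss to follow-up, study withdrawal or end of study.

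**The concern.** The secondary question is whether survival differs by allocated schedule. The FA set answers a narrower one: survival among eligible patients who received a first fraction. Not starting palliative radiotherapy is plausibly linked to prognosis, since death or deterioration is a natural reason for it.

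The allocation is known to patient and physician. Arm A begins with one attendance and arm B with five. A patient who deteriorates between randomisation and treatment might still be given a single fraction, yet be judged to need a modified five-fraction course. Under section 6.5 that patient is discontinued before starting and so falls outside the FA set. Losses could equally run the other way. Nothing in the design ensures that they balance.

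The restriction is not forced by the data. Death requires no visit or questionnaire, so the difficulty that limits the symptom endpoint does not arise. At stake is whether a comparison that conditions the treatment recommendation keeps the protection of randomisation.

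**Working it through.** **The plan's own figures.** The only sample size in the protocol is for the primary endpoint. With SD 2, margin 1, one-sided 2.5% and 85% power, the normal approximation gives n per arm = 2 × 2² × (1.960 + 1.036)² / 1² = 71.8, so 72 per arm or 144. With 73 per arm the t distribution gives power 0.851, which matches 146. Dividing by 0.75 gives 195, against 200 stated. None of this depends on the survival set. The protocol has no survival figure to reproduce.

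**Who is lost.** The ITT set needs randomisation and consent. The FA set adds eligibility and one delivered fraction. The difference is (a) patients with no fraction and (b) patients classed as ineligible. An arm B patient who starts and then stops stays in the FA set.

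**How many could die before starting (assumption).** The documents give no rate. Take exponential survival with the medians of the earlier cohorts cited in 2.2.2.2 and 2.2.2.3 (9 months rectal, 20 months prostate). Then P(death by d days) = 1 − exp(−ln 2 × d / (median × 30.44)).

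- 14 days: 3.5% (9 months), 1.6% (20 months).
- 28 days: 6.8% (9 months), 3.1% (20 months).

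The 28-day values are upper bounds. In the Schedule of Activities, 28 days covers screening plus preparation, and randomisation falls within preparation. Selection for expected survival over 12 weeks should lower all four figures.

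**Effect on the hazard ratio (assumption).** Take 100 per arm, true HR 1, and censoring uniform over 12 to 48 months. With λ = ln 2 / median, expected deaths per arm are

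D = 100 × [1 − (e^(−12λ) − e^(−48λ)) / (36λ)].

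- Median 9: λ = 0.0770, D = 100 × [1 − (0.397 − 0.025)/2.773] = 86.6.
- Median 20: λ = 0.0347, D = 100 × [1 − (0.660 − 0.189)/1.248] = 62.3.

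As the worst case, let the excluded patients be the earliest deaths. They carry almost no person-time, so excluding a patients from A and b from B gives HR (A vs B) ≈ (D − a)/(D − b). A simulation of the events-per-person-time ratio (5,000 repeats) is shown beside it.

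| Lost A / B | Median 9: formula | Simulated | Median 20: formula | Simulated |
|---|---|---|---|---|
| 2 / 2 | 1.00 | 1.00 | 1.00 | 1.00 |
| 0 / 4 | 86.6/82.6 = 1.05 | 1.05 | 62.3/58.3 = 1.07 | 1.07 |
| 1 / 5 | 85.6/81.6 = 1.05 | 1.05 | 61.3/57.3 = 1.07 | 1.07 |
| 2 / 8 | 84.6/78.6 = 1.08 | 1.07 | 60.3/54.3 = 1.11 | 1.10 |

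A separate Cox simulation (9-month median, 2,500 per arm) excluded frail patients with a median of 1 to 2 months instead of strictly the earliest deaths. It gave 1.03 to 1.05 for losses of 0% vs 3%, 0% vs 5% and 2% vs 8%, and 1.09 to 1.10 for 0% vs 10%. If the larger loss is in arm A, the ratio moves below 1 and flatters the short course.

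**Whether renaming the set is enough.** Suppose the set becomes ITT but sections 6.5, 7.2 and the censoring rule stay. A patient discontinued before the first fraction is then censored near time zero, adding no death and almost no person-time. D falls by one and person-time hardly changes, which is the same arithmetic as exclusion. The discontinuation and censoring rules must therefore change too.

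**Time origin.** A footnote to the Schedule of Activities counts all follow-up from completed radiotherapy. A patient who never starts has no such date, so an ITT survival analysis needs randomisation as its origin.

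**The case against.** Several points on the other side stand.

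- A reader might infer that survival will be examined only in the FA set. The protocol says main analyses, and section 9.5 leaves technical detail to an analysis plan that is not shown, so a supportive ITT analysis is not ruled out. The choice of main set is nevertheless fixed in 9.4.
- A reader might infer that patients will be re-judged ineligible after randomisation using outcome information, since one criterion is "Expected survival" beyond 12 weeks. The protocol describes no such step. Section 8 requires eligibility to be confirmed from completed screening evaluations, and the Schedule of Activities places the eligibility check and randomisation in the same period. What can be said is that the protocol does not limit eligibility exclusions to pre-randomisation data or require them to be judged blind to arm.
- The route to bias is narrow. One fraction secures FA membership, and the first attendance is a common step in both arms. Only loss before that point matters.
- The larger hazard ratio shifts need imbalances that no document supports. Assuming 120 to 180 deaths, the 95% interval for the hazard ratio spans a factor of exp(2 × 1.96/√120) = 1.43 to exp(2 × 1.96/√180) = 1.34 each way, well beyond a shift of a few percent.
- Survival has no margin, so a small shift may not change the recommendation.

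These points limit the size of the problem. They do not give a reason to prefer the FA set for survival, and the protocol offers none.

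**Conclusion.** The point holds as a weakness in the choice of main analysis set. Section 9.4 fixes a survival comparison with post-randomisation exclusions in an open-label trial, although an ITT set is already defined and comparable survival conditions the recommendation. The documents do not support a claim that the result will be biased, nor any particular size. With few or balanced losses the effect is about zero. With the moderate imbalances assumed above it is roughly 3% to 8% on the hazard ratio, and it reaches about 10% only under the most extreme assumptions. These figures rest on exponential survival, the cited medians, a true hazard ratio of 1 and assumed loss patterns. The direction depends on which arm loses more frail patients. The change is worth making because it is cheap and removes the dependence on those unknowns. It does not call the design or sample size into question.

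**What to change.** 1. In 9.4, base the main analysis of overall survival on the ITT set, by allocated arm and with time from randomisation. Keep the FA set as a sensitivity analysis.
2. In 6.5, 7.2 and the survival censoring rule in 1.1 and 4.1, state that patients who do not start radiotherapy, or who are discontinued from the study, remain in vital-status follow-up unless they withdraw consent for it, and are not censored at discontinuation.

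The cost is a short amendment to these sections, matching text in the analysis plan, and tracking vital status for the patients concerned. No extra patients or visits are needed, and the sample size does not change. A small downside is that a few untreated patients slightly dilute any treatment-related survival difference; the FA sensitivity analysis will show how much.

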## **9.5. Statistical analyses**

A statistical analysis plan (SAP) will be finalized prior to the database lock, and it will include a more technical and detailed description of the statistical analyses described in this section, which gives a brief summary of the planned statistical analyses of the primary endpoint and secondary endpoints.

### **9.5.1. General Considerations**

A difference between study arms is denoted as statistically significant if the P value is less than the prespecified significance level of 5%. Correspondingly, a confidence level of 95% will be used for the two-sided confidence interval (CI) linear regression models.

### **9.5.2. Primary Endpoint**

Linear regression models will be employed to estimate the difference between the two treatments (change in average target symptom intensity from baseline to the follow up at 12 weeks). We will conclude that 1-2 fractions of 8 Gy (Arm A) is non-inferior to 5 fractions of 5 Gy (Arm B) if the lower bound of the two-sided 95 % confidence interval is above the NIM of -1 (negative values indicate worse outcome for arm A).

Statistical tests for interaction in multivariable linear regression model will be used to assess heterogeneity of radiotherapy treatment effect across different target symptoms.

### **9.5.3. Secondary Endpoint**

Data will be reported as means, 95 % confidence intervals, medians or frequencies as appropriate CTCAE:

For all; comparison between the two study arms

1. Number of events any grade, any CTCAE category
2. Number of events grade 1-2 vs grade 3-4, any CTCAE-category
3. Number of events any grade, by CTCAE-category
4. Number of events grade 1-2 vs grade 3-4, by CTCAE category
5. Number of patients with event, any CTCAE category
6. Number of patients with events grade 1-2 vs grade 3-4, any CTCAE category
7. Number of patients with events any grade, any CTCAE category
8. Number of patients with grade 1-2 vs grade 3-4 event, by CTCAE category

CTCAE categories: Gastrointestinal, urinary, reproductive system, constitutional, other

Overall survival:

Kaplan Meier- curves compared with the log-rank test and univariable and multivariable Cox proportional-hazards regression analyses

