#### **Secondary objective**

*To assess the efficacy of 1-2 fractions of 8 Gy compared to 5 fractions of 5 Gy with respect to:*

- Physician-reported toxicities

Endpoint: Bladder and bowel toxicity after 4, 12 and 52 weeks of follow-up

Assessment: Common Terminology Criteria for Adverse Events (CTCAE) v 5.0

- Survival

Endpoint: Overall survival (OS) assessed at the end of study

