### **8.3.2. Physician-assessed toxicity CTCAE**

Common Terminology Criteria for Adverse Events version 5.0.

Assessed baseline and after 4 weeks, 12 weeks and 52 weeks of follow-up.

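### None of the eight CTCAE comparisons in section 9.5.3 uses the baseline grade that is collected, so persisting tumour symptoms can be counted as any-grade toxicity

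*Protocol*

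**What the plan says.** The secondary toxicity endpoint in protocol section 3 is "Endpoint: Bladder and bowel toxicity after 4, 12 and 52 weeks of follow-up". Section 8.3.2 has CTCAE "Assessed baseline and after 4 weeks, 12 weeks and 52 weeks of follow-up", and the schedule of activities (section 1.2) agrees.

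Section 9.5.3 lists eight comparisons between the arms. Items 1-4 count events, the first being "Number of events any grade, any CTCAE category". Items 5-8 count patients; item 7 is "Number of patients with events any grade, any CTCAE category" and item 8 is "Number of patients with grade 1-2 vs grade 3-4 event, by CTCAE category". The categories are "CTCAE categories: Gastrointestinal, urinary, reproductive system, constitutional, other".

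Section 5.1 requires "Tumor-related symptoms within the following five predefined categories: pain, bleeding, bowel dysfunction, lower urinary tract dysfunction and vaginal dysfunction", with an average severity of at least 4 on the 0-10 scale. Section 9.2 makes the recommendation of the short schedule depend on non-inferior symptom relief and on whether "comparable QoL, toxicities and OS can be proved 12 weeks after the intervention".

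**The concern.** The symptoms that qualify a patient for the trial lie largely in the organ systems in which toxicity is then counted. A patient who enters with tumour-related bowel dysfunction and still has it at 12 weeks carries a gastrointestinal CTCAE grade that radiotherapy did not cause. If such items count, the any-grade totals rise in both arms for a reason unrelated to treatment, and a real difference in radiation toxicity is harder to see.

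The direction matters. The protocol sets no margin for toxicity, but comparable toxicity is part of the case for the short schedule. Noise from symptoms present at entry makes the arms look alike and so favours that conclusion.

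Two smaller defects sit in the same list. Half the items take the event as the unit, although several events in one patient are not independent. And one item is a duplicate, which leaves out a count that the bladder and bowel endpoint needs.

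**Working it through.** **The list, item by item**

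| Item | Unit | Grade | Category | Uses baseline |
|---|---|---|---|---|
| 1 | event | any | pooled | no |
| 2 | event | 1-2 vs 3-4 | pooled | no |
| 3 | event | any | by category | no |
| 4 | event | 1-2 vs 3-4 | by category | no |
| 5 | patient | not split | pooled | no |
| 6 | patient | 1-2 vs 3-4 | pooled | no |
| 7 | patient | any | pooled | no |
| 8 | patient | 1-2 vs 3-4 | by category | no |

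Items 1-4 run through the four combinations of grade and category. Items 5-8 follow the same order, except that item 7 says any category where the pattern calls for by category. It repeats item 5, and any-grade patients by category is not listed.

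**Where grade 1-2 counts come from.** Section 8.5.1 limits adverse event collection to grade 3 and above and serious events. Grade 1-2 counts can therefore come only from the visit grading of section 8.3.2. Appendix 3 (section 10.3.1) excludes pre-existing conditions that do not worsen, and expected symptoms of the disease, but as part of the adverse event definition. Nothing ties that exclusion to the visit grading.

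**Size.** The protocol gives no toxicity rate and no power for this comparison, so there is no toxicity figure to reproduce. Its only sample size is for the primary endpoint: 146 evaluable, 73 per arm, SD 2, margin 1. That figure reproduces: 1/(2·√(2/73)) = 3.02, and Φ(3.02 − 1.96) = 0.856; the exact t calculation gives 0.851, against the stated 85%. A round 75 per arm is used below.

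Assumptions, none from the documents:
- New toxicity p = 15% in one arm and 30% in the other, among patients without the item at baseline.
- A share b in each arm has the item at baseline and still has it at follow-up.
- At first, patients with the item at baseline do not worsen.

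Formulas:
- Baseline items counted: rate = b + (1 − b)p.
- Only new toxicity counted: rate = (1 − b)p.
- SE = √[(r₁(1 − r₁) + r₂(1 − r₂))/75].
- Two-sided 5% power = Φ(d/SE − 1.96) + Φ(−d/SE − 1.96), where d is the difference in rates.

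| b | Rates, baseline counted | SE | Power | Rates, new only | SE | Power | d |
|---|---|---|---|---|---|---|---|
| 40% | 49% vs 58% | 0.0811 | 19.9% | 9% vs 18% | 0.0553 | 37.0% | 9 points |
| 60% | 66% vs 72% | 0.0754 | 12.5% | 6% vs 12% | 0.0465 | 25.2% | 6 points |
| 80% | 83% vs 86% | 0.0590 | 8.0% | 3% vs 6% | 0.0338 | 14.4% | 3 points |

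The absolute difference is the same under both counts. What changes is the noise and the relative contrast: the rate ratio is 2.0 when only new toxicity counts, and 58/49 = 1.18, 72/66 = 1.09 and 86/83 = 1.04 when baseline items count.

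If patients with the item at baseline also worsen, at the same 15% and 30%, a count of new or worsened items gives 15% vs 30% in all patients, whatever b is. Then d = 15 points, SE = 0.0671 and power is about 60%. The raw any-grade count stays at the 20, 12 and 8% above, because worsening of an item already present does not change whether it is present.

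**Event as unit.** With m events per patient and within-patient correlation 0.3 (assumed), the variance is inflated by 1 + 0.3(m − 1). A nominal 5% test that ignored this would have true error 2[1 − Φ(1.96/√(1 + 0.3(m − 1)))] = 8.6%, 12.1% and 15.5% for m = 2, 3 and 4.

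**The case against.** The strongest reply is that section 9.5 calls itself a brief summary and leaves technical detail to a statistical analysis plan, where event definitions, baseline handling and clustering usually sit. Had section 9.5.3 stayed general, that would settle the matter. But it lists the eight comparisons, so what it lists is open to comment, and the item 7 slip is visible on the page.

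Four stronger readings are tempting, and the documents do not support them:
- *That the protocol plans to count entry symptoms as toxicity.* It does not say so. The word event is undefined in section 9.5.3, and Appendix 3 points the other way for adverse events. The defect is an ambiguity that permits such counting.
- *That most patients have a baseline item in the bladder and bowel categories.* Section 5.1 requires one qualifying symptom of any of five kinds. No baseline prevalence by category is given, which is why b is varied.
- *That using baseline would restore the 60% power of a population with no baseline items.* It would not, unless patients with the item at baseline also worsen at the assumed rates. With new toxicity only, power is 37, 25 or 14%.
- *That counting events hides differences between arms.* Treating events as independent overstates precision and tends to create differences. Section 9.5.3 also names no event-level test, so the error rates above apply only if one is used.

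It also stands that four items count patients and four split grade 1-2 from grade 3-4. The grade 3-4 counts are less exposed to baseline symptoms, though not immune. Any-grade patients by category could largely be derived from the data behind item 8, so the duplicate is most likely a wording slip.

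**Conclusion.** The point holds in limited form. A baseline CTCAE grade is collected, none of the eight listed comparisons uses it, and nothing in the protocol prevents persisting tumour symptoms from entering the grade 1-2 and any-grade counts. The effect is added noise and a pull toward apparent comparability, on a question that bears on the recommendation of the short schedule.

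Under the assumed rates, counting baseline items roughly halves power (20, 12 and 8% against 37, 25 and 14% for b of 40, 60 and 80%) with no change in the absolute difference. The loss is larger if patients with the item at baseline can also worsen. These figures rest on assumed toxicity rates, an assumed b that persists equally in both arms, and 75 per arm. They show direction and order of size only. Power for toxicity is low in all the new-only scenarios, so the fix improves the comparison without making it decisive.

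The event-as-unit issue and the duplicated item are separate and smaller. The primary endpoint is not affected.

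**What to change.** In section 9.5.3:
- Define a toxicity event as a CTCAE grade above that patient's own baseline grade for the same term.
- Make the per-patient worst such grade, by category, the main between-arm comparison, with gastrointestinal and urinary first because they carry the secondary endpoint.
- Keep event counts and raw any-grade counts as descriptive tables.
- Correct item 7 to read by CTCAE category.

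This is wording only. Baseline CTCAE is already in the schedule, so no new data or visits are needed. The small cost is that raw any-grade counts become descriptive.
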